### Objectives

The following are the objectives of this study:

Objective 1: to assess the efficacy of ASB in infrabony defects at 6 months after surgery with regard to radiographic bone fill, reduction in probing pocket depth (PPD), and increase in clinical attachment level (CAL).Objective 2: to assess the efficacy of autologous PRF in conjunction with OCP-DBBM in infrabony defects at 6 months after surgery with regard to radiographic bone fill, reduction in PPD, and increase in CAL.Objective 3: to assess the efficacy of ASB and autologous PRF in conjunction with OCP-DBBM in infrabony defects at 6 months after surgery with regard to radiographic bone fill, reduction in PPD, and increase in CAL.

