where α=.05, β=.1, SD in group 1 (σ1) is 0.83, mean in group 1 (μ_1_) is 0.522, SD in group 2 is (σ2) 0.044, mean in group 2 (μ_2_) is 0.42, and ratio (group 2 to group 1)=1. The total sample size required was 10 participants per group, as indicated by the calculation [13].

Inclusion and exclusion criteria for patient screening for infrabony defects.

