#### Debridement and Root Surface Management

The osseous defect will be debrided off the granulation tissue using hand instruments (Gracey curettes, Hu-Friedy) followed by ultrasonic instruments (EMS, Minipiezon), thus exposing the root surface, alveolar bone, and periodontal ligament. Any granulomatous tissue or epithelium adherent to the inner surface of the flap or papillae will be judiciously removed, taking care not to overthin the flap. The root surfaces will be planned to remove plaque and calculus by using ultrasonic instruments, followed by hand instrumentation. The root surfaces will be planed until a smooth and hard consistency is obtained.

At this stage, direct measurements of the vertical bone defects (BDs) and the number of bony walls present will be recorded with the UNC-15 probe. If the BD depth is ≥3 mm vertically, final participant eligibility will be confirmed.

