### Statistical Analysis

#### Power

PI, papillary bleeding index, PPD, relative attachment level, and relative gingival marginal level will be calculated by mean and SD values. Statistical tests such as the paired 1-tailed *t* test or Wilcoxon signed-rank test for within-group comparison and the ANOVA or Kruskal-Wallis test for between-group comparison are typically used to assess clinical and radiographic outcomes. The choice of test depends on whether the data follow a normal distribution. The difference between radiographic bone fill, PPD, CAL and relative gingival margin level will be considered significant only if *P*<.05.

The study population will be divided into 2 groups: group 1 (ASB) and group 2 (autologous PRF with OCP-DBBM). There are no subgroups in the study.

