### Radiographic Analysis

The infrabony defect sites will be investigated with CBCT at baseline and 6 months postoperatively. The CBCT analysis will include the measurement of BD height (CEJ–base of the defect), level of alveolar crest (AC; CEJ–AC), BD depth (AC-BD), and the mesiodistal (MD) and buccolingual BD width. The landmark of the base of the defect will be the lowest discontinuous point of the periodontal ligament. A line perpendicular from the AC to the root surface will be drawn, and the intersection point across the root surface will be termed as AC'.

Infrabony defect depth: The distance from the point AC' to the base of the defect (AC'-BD). MD width of the infrabony defect (AC-AC): The distance from the point AC' to the AC. The buccolingual width of the defect will be measured by selecting the innermost and most coronal points of the buccal and lingual AC on the axial plane, and calculating the horizontal distance between these two points. A 1.00-mm incremental slice thickness will be used in this study’s investigation, as smaller slices decrease the image resolution. In the oblique view, the x-, y-, and z-axes will be sequentially analyzed to locate the most apical point of the BD or the most coronal aspect of the defect-associated AC [6].

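### The between-group test is left to a normality check on about 10 values per arm, and the tests named do not adjust for the baseline values the trial collects

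*Protocol article*

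**What the plan says.** Under Statistical Analysis (Power), the protocol article says "ANOVA or Kruskal-Wallis test for between-group comparison are typically used to assess clinical and radiographic outcomes" and then "The choice of test depends on whether the data follow a normal distribution". It names no normality test, no threshold and no covariate. It does not say whether the arms are compared on 6-month values or on changes. Sidedness is given only for the within-group test, "paired 1-tailed *t* test or Wilcoxon signed-rank test for within-group comparison". The significance rule is "will be considered significant only if *P*<.05".

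Baseline data are collected:
- Radiographic Analysis: "The infrabony defect sites will be investigated with CBCT at baseline and 6 months postoperatively".
- Evaluation Outcomes: clinical measures are taken on the day of surgery and at 6 months.
- Debridement and Root Surface Management: "direct measurements of the vertical bone defects (BDs) and the number of bony walls present will be recorded".

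The primary outcome is radiographic bone fill at 6 months, for which no formula is given. Two secondary outcomes, attachment gain and pocket depth reduction, are worded as changes. The objective covering both arms reads "Objective 3: to assess the efficacy of ASB and autologous PRF in conjunction with OCP-DBBM in infrabony defects" and states no contrast between them.

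**The concern.** The comparison of the two arms is the only randomized evidence in the trial, so its analysis should be fixed in advance. With two arms, one-way ANOVA is a two-sample t test of means and Kruskal-Wallis is a rank-sum test. They answer different questions. If the data choose between them, a reader cannot know beforehand what the primary result will estimate.

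The tests named also leave baseline values out of the model. With 10 per arm, a chance difference in baseline defect depth can be sizeable. A pre-set baseline-adjusted model would remove its influence and usually sharpen the estimate.

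**Working it through.** **1. The plan's own figure.** Recruitment gives alpha .05, beta .1, SDs 0.83 and 0.044, means 0.522 and 0.42, and 10 per group.
- n = (0.83² + 0.044²)(1.960 + 1.282)² / 0.102² = 698 per group (two-sided, 90% power), not 10.
- With 0.083 in place of 0.83, n is 9. A decimal slip is plausible but cannot be proved.
- This is a separate problem. It matters here only because no power baseline can be taken from the plan without choosing a reading.

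**2. How the normality rule behaves at 10 per arm.** Assumption, since no test is named: Shapiro-Wilk at 5% in each arm, and Kruskal-Wallis if either rejects. Simulation with 20,000 trials and no treatment effect:

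| True distribution | Switches to Kruskal-Wallis | Type I error of the two-stage procedure |
|---|---|---|
| Normal | 10% | 5.0% |
| t, 3 df | 34% | 5.1% |
| Lognormal, sigma 0.5 | 42% | 5.8% |
| Exponential | 69% | 5.9% |

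In a single sample of 10, Shapiro-Wilk detects the lognormal 24% of the time and the exponential 45%. For moderately skewed data, which test gets reported is close to a coin toss. The error rate barely moves.

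**3. Precision of the three possible analyses.** Let r be the correlation between baseline and 6-month value, with equal SDs at the two times. The article gives no r; the range 0 to 0.7 is assumed.
- ANCOVA variance relative to 6-month values: 1 − r².
- ANCOVA variance relative to change scores: (1 − r²) / [2(1 − r)] = (1 + r)/2.
- Estimating the slope with 18 within-arm degrees of freedom multiplies both by about 1 + 1/16 = 1.0625 for a normal covariate.

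Power is simulated at 10 per arm for a true effect of 1 SD, 10,000 trials. That effect is illustrative and is not in the plan.

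| r | 1 − r² | (1 + r)/2 | Power: 6-month values | Power: change | Power: ANCOVA |
|---|---|---|---|---|---|
| 0 | 1.00 | 0.50 | 55% | 32% | 53% |
| 0.3 | 0.91 | 0.65 | 55% | 43% | 57% |
| 0.5 | 0.75 | 0.75 | 57% | 56% | 66% |
| 0.7 | 0.51 | 0.85 | 57% | 79% | 83% |

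The 6-month column does not truly depend on r; its 55 to 57% spread is simulation error. With the 1.0625 factor, ANCOVA has the smaller variance than 6-month values once r exceeds about 0.24 (r² > 1/17), and than change scores while r is below about 0.88 (1 + r < 32/17).

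**4. Chance imbalance.** If allocation is not stratified on baseline depth, the SD of the difference in baseline means is √(2/10) = 0.447 baseline SDs. The probability of a difference above 0.5 SD is 2[1 − Φ(0.5/0.447)] = 26%. Among those trials only, with no treatment effect, the simulated false-positive rate was:
- r=0.5: about 9 to 10% for 6-month values, about 9% for change scores, about 5 to 6% for ANCOVA.
- r=0.7: about 13 to 14%, about 8% and about 5%.

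Over all randomizations, each of the three stays at about 5%.

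**5. What adjustment does to the plan's own sample size.** With the printed SDs, the required n falls from 698 to 635, 524 and 356 at r = 0.3, 0.5 and 0.7, and power at 10 per arm stays at 7 to 8%. If 0.083 was meant, power at 10 per arm rises from 90% to 92%, 96% and 99%.

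**The case against.** **The baseline may already be used.** A reader might infer that the trial throws its baseline measurements away. The article does not support that. Attachment gain and pocket depth reduction are changes, and bone fill implies a change between two scans. A comparison of changes uses the baseline, though less efficiently, and it over-corrects an imbalance. Only a comparison of 6-month values would ignore the baseline, and the article leaves this open.

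**The unadjusted tests are valid.** A reader might also infer a biased result or a materially inflated error rate. Neither follows. Chance imbalance is already reflected in the standard error, and the two-stage error rate is at most about 5.9%. The rates in step 4 of the working are conditional on an imbalance having occurred.

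**Covariates may be left to an analysis plan.** The sentence lists typical tests, and an unseen plan could add a covariate. This has force against treating the missing covariate as an error. It does not dispose of the normality rule, which the article states outright and which a plan fixing one model would have to override.

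**The gain is unknown.** Neither r nor the form of bone fill is given, and the planning means carry no units. The method of allocation is not described either. All of this stands, which is why a range is shown and the 26% is conditional.

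**The third objective is a wording matter.** The title and the analysis section make the comparative intent clear.

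**Conclusion.** The concern holds in a limited form. The article states a data-driven choice between two unadjusted tests, so the primary analysis and what it estimates are not fixed. A single pre-set ANCOVA on baseline is the better method. It beats a comparison of 6-month values at moderate or high r, and it beats a comparison of changes throughout the assumed range of 0 to 0.7.

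Against 6-month values the size runs from a loss of 2 to 3 power points at r=0, through little gain at 0.3, to a substantial gain at 0.5 or more. These figures rest on an illustrative effect of 1 SD, equal SDs at both times, normal data and one independent defect per participant. The issue is one of precision and pre-specification. It is worth changing but does not invalidate the trial.

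**What to change.** - State one confirmatory analysis: a two-sided ANCOVA of 6-month CBCT defect depth on arm, with baseline CBCT defect depth as covariate, reported as an adjusted mean difference with 95% CI.
- Define bone fill to match, as the change in that depth in mm. With baseline in the model, change and 6-month depth then give the same treatment effect apart from sign. This would not hold for percentage fill.
- Use the same model, each with its own baseline, for pocket depth, attachment level and gingival margin level.
- Drop the normality-based choice. Keep a rank or permutation test as a sensitivity analysis only.
- Reword the third objective as a comparison of the two arms on bone fill.
- Say whether each participant contributes one defect. The Abstract counts 20 defects, Recruitment counts 10 participants per group, and the inclusion criteria allow one or two defects. If some contribute two, the model must allow for it.

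The cost is wording and one degree of freedom, with a slight loss of power if r is near zero. No new data are needed. The sample-size calculation needs its own correction, which adjustment does not supply.

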#### Evaluation Outcomes

Clinical measurements to be recorded on the day of surgery and 6 months after surgery are PI [14], papillary bleeding index [15], PPD, relative attachment level, and relative gingival marginal level. Periodontal charting on a specially designed form and CBCT will also be documented.

### PI Assessment

Plaque will be assessed on the labial or buccal and lingual surfaces of all the teeth after using a disclosing agent (Table 1) [14].

**Table 1 table1:** Score criteria for the plaque index.

Score	Criteria
0	No plaque
1	Separate flecks of plaque at the cervical margin of the tooth
2	A thin, continuous band of plaque (up to 1 mm) at the cervical margin
3	A band of plaque wider than 1 mm but covering less than one-third of the crown
4	Plaque covering at least one-third but less than two-thirds of the crown
5	Plaque covering two-thirds or more of the crown

### Calculations of PI

The sum of the scores around each tooth was divided by 2 to obtain the PI score for the tooth. The PI score per person will be obtained by totaling all the plaque scores and dividing by the number of teeth examined.

### Papillary Bleeding Index

A periodontal probe will be carefully inserted into the gingival sulcus at the base of the papilla on the mesial aspect and then moved coronally to the papilla tip [15]. This will be repeated on the distal aspect of the same papilla. The intensity of any bleeding thus provoked will be recorded on a 0 to 4 scale (Table 2).

**Table 2 table2:** Score criteria papillary bleeding index.

Score	Criteria
0	No bleeding
1	A single discrete bleeding point appears
2	Several isolated bleeding points or a single fine line of blood appears
3	The interdental triangle fills with blood shortly after probing
4	Profuse bleeding occurs after probing; blood flows immediately into marginal sulcus

### Calculations of Papillary Bleeding Index

Each papilla will be scored according to the aforementioned criteria. The sum of all scores will be divided by the number of papillae examined to obtain the papillary bleeding index score per person.

### Probing Measurements

Both treatment groups will be subjected to recordings to measure PPD, relative CAL, and relative gingival margin level at 6 sites of the selected teeth. Measurements will be carried out using a UNC-15 calibrated periodontal probe (University of North Carolina) at the mesiobuccal, mesiolingual, distobuccal, distolingual, midbuccal, and midlingual points of the selected tooth. After measurement, only the deepest marking per defect will be considered for study purposes. After the fabrication of the acrylic stent, probing measurements will be recorded at baseline and 6 months postoperatively.

The UNC-15 probe will be positioned on the prepared groove of the acrylic stent. The probe will be placed with its tip at the gingival marginal level, and the distance between the gingival margin and the lower border of the stent will be measured as the relative gingival margin level. Then, the probe will be positioned at the bottom of the pocket, and the distance from the lower border of the stent to the bottom of the pocket will be noted as the relative CAL. PPD will be measured by subtracting the relative gingival margin level from the relative CAL. The width of keratinized gingiva will be calculated from the lowest point of the mucogingival junction to the crest of the gingival margin using the UNC-15 probe.

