### Primary Outcome: Radiographic Bone Fill

The primary outcome measured in the study is radiographic bone fill at 6 months after surgery. This outcome is crucial as it indicates the extent of bone regeneration achieved through the different treatment modalities being tested.

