### Secondary Outcomes

In addition to the primary outcome, the study also assesses secondary outcomes, which include the following:

CAL gain, which measures the improvement in the attachment of the periodontal tissue to the tooth, indicating successful regeneration.PPD reduction, which is used to evaluate the decrease in the depth of periodontal pockets, which is a sign of improved periodontal health.Relative gingival marginal level, which has been documented to assess the health of the gingival tissue surrounding the teeth.

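### The probing rule keeps the deepest site but does not say that the 6-month value comes from the site chosen at baseline, so pocket-depth reduction and attachment gain may be understated

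*Protocol article*

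**What the plan says.** All the relevant text is in the protocol article.

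- **What is probed (Probing Measurements).** PPD, "relative CAL, and relative gingival margin level at 6 sites of the selected teeth" are recorded in both treatment groups.
- **What is kept (same section).** "After measurement, only the deepest marking per defect will be considered for study purposes".
- **When (same section, the next sentence).** "After the fabrication of the acrylic stent, probing measurements will be recorded at baseline and 6 months postoperatively".
- **How the probe is placed (same section).** "The UNC-15 probe will be positioned on the prepared groove of the acrylic stent".
- **How PPD is obtained (same section).** "PPD will be measured by subtracting the relative gingival margin level from the relative CAL".
- **What the readings feed (Secondary Outcomes).** "CAL gain, which measures the improvement in the attachment of the periodontal tissue to the tooth" and "PPD reduction, which is used to evaluate the decrease in the depth of periodontal pockets". Relative gingival margin level is the third secondary outcome.
- **What they do not feed (Primary Outcome).** "The primary outcome measured in the study is radiographic bone fill at 6 months after surgery". This is measured on CBCT.

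The text does not say whether the deepest site is chosen once, at baseline, or again at 6 months.

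**The concern.** PPD reduction and CAL gain are changes, so they describe healing only if both values come from the same place. The selection rule is attached to the act of measuring, and measuring happens twice. Applied at each visit, it subtracts the maximum at 6 months from the maximum at baseline. Once the defect site has healed, another site may be the deepest and supply the second value. Even where true depths are equal, the largest of several readings with error lies above the true depth.

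Both effects push the 6-month value up and the recorded improvement down. If one treatment heals the defect further than the other, the better arm loses more of its gain, because its defect site more often drops below a neighbour. With 10 defects per group, such a loss could hide a real difference in the clinical outcomes.

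**Working it through.** The plan gives no figure for this point to reproduce: no probing error, no site-to-site variation and no expected change in PPD or CAL. All depths and error SDs below are therefore assumptions, in mm. Each scenario used 200,000 simulated teeth or defects.

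**The mechanism by hand.** Suppose the defect site reads 7 at baseline and 4 at 6 months, and another site reads 5 both times.
- Same site: 7 − 4 = 3.
- Deepest at each visit: 7 − 5 = 2.

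**Formulas.** With readings b (baseline) and p (6 months) over the competing sites, and i the deepest site at baseline:
- Fixed site: change = b[i] − p[i].
- Re-selected: change = max(b) − max(p).

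**Model A: every tooth has the same true profile; error SD 0.5 and 0.8.** The shortfall is the true change at the deep site minus the re-selected mean.

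| Baseline to 6 months | True change | Re-selected mean | Shortfall | Site differs |
|---|---|---|---|---|
| Six sites: (7, 5.5, 4, 4, 3.5, 3.5) to (4, 4, 3.5, 3.5, 3.5, 3.5) | 3.0 | 2.61; 2.32 | 0.39; 0.68 | 66%; 72% |
| Two sites, tied after healing: (7, 5.5) to (4, 4) | 3.0 | 2.72; 2.60 | 0.28; 0.40 | 50%; 50% |
| Six sites, defect site stays 1 mm deeper: 6-month (4.5, 3.5, 3, 3, 3, 3) | 2.5 | 2.47; 2.34 | 0.03; 0.16 | 13%; 38% |
| Two sites, defect site stays 1 mm deeper: 6-month (4.5, 3.5) | 2.5 | 2.48; 2.43 | 0.02; 0.07 | 9%; 25% |

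The fixed site in the first row gives 3.01 and 3.06.

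**Model B: true depths vary between sites (SD 0.8) and so does healing (SD 0.4); error SD 0.3, 0.5 and 0.8.** Bias is measured against the true change at the site deepest at baseline.

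| Mean baseline to mean 6 months | Fixed-site bias | Re-selected bias |
|---|---|---|
| One deep site: (7, 5, 4, 4, 3, 3) to (3.5, 3.5, 3.5, 3.5, 3, 3) | +0.02; +0.06; +0.22 | −0.92; −0.94; −0.95 |
| Two deep sites, large gain: (7, 6.5, 4, 4, 3, 3) to (3.5, 3.5, 3.5, 3.5, 3, 3) | +0.05; +0.14; +0.34 | −0.62; −0.65; −0.71 |
| Two deep sites, moderate gain: (7, 6.5, 4, 4, 3, 3) to (5, 4.5, 3.5, 3.5, 3, 3) | +0.06; +0.14; +0.33 | −0.13; −0.14; −0.18 |
| Two defect sites only: (7, 6.5) to (3.5, 3.5) | +0.05; +0.14; +0.30 | −0.09; −0.08; −0.07 |

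In the last row the means are equal at 6 months, but individual true depths differ, so exact ties do not occur. Across Model B the re-selected site differs between visits in 24% to 76% of defects.

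**Between groups (Model B, one deep site, six sites competing).**
- Equal arms: the simulated difference is 0.00 to two decimals under both rules, apart from simulation error of at most 0.005.
- Second arm heals 1 mm less at the deep site, to (4.5, 4, 3.5, 3.5, 3, 3): the fixed site shows a difference of 0.97, 0.95 and 0.90. Re-selection shows 0.44, 0.43 and 0.40.

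**Regression to the mean.** The positive fixed-site bias, +0.02 to +0.34, arises because the site was picked for a high baseline reading. It enters the within-group paired tests named under Statistical Analysis. It was the same in both arms of the comparison above.

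**The case against.** The strongest reply is that re-selection is an inference. The section never says that the choice is repeated at 6 months. The grooved stent exists to return the probe to a repeatable position, and choosing the deepest site once and re-probing it there fits the text. The rule also works per defect, which may confine the choice to sites adjoining the defect. A neighbour elsewhere on the tooth could then never replace the defect site. The large shortfalls come from profiles in which the 6-month depths are nearly tied. Finally, a condensed article may leave the index site to the full protocol or the charting form.

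Much of this stands. A reader might infer that the trial will compare different sites and that the bias is established; the text shows only that it leaves this open. The reply does not close the gap, though. A groove fixes where the probe goes at a given point, not which of six points supplies the analysed value, and several points can adjoin one defect. Nor is this only omitted detail: the article states the reduction rule and leaves it open where a change score depends on it.

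Three further inferences are tempting and not supported.
- **That the outcomes become noisier.** In the first Model A scenario at error SD 0.5, the SD of the change is 0.60 mm re-selected against 0.70 mm fixed. There is no general increase.
- **That PPD would stop equalling relative CAL minus relative margin level.** This needs the three readings to be maximised separately. The text speaks of a single deepest marking and does not say that.
- **That the rule could create a difference between equal groups.** It applies identically to both, and the simulation shows none.

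**Conclusion.** The point holds as an unfixed index site with a possible bias, not as a demonstrated one. If the deepest site is re-selected at 6 months, PPD reduction and CAL gain are understated and a true group difference can be attenuated; in the scenario examined, about 1 mm became about 0.4 mm.

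The within-group shortfall is about 0.02 to 0.2 mm when the defect site stays deepest or only two defect sites compete without a tie. It is about 0.3 to 0.95 mm when the defect site heals to or near its neighbours' level. These ranges rest on assumed depth profiles and on error SDs of 0.3 to 0.8 mm. They were simulated for pocket depth; the same mechanism applies to relative CAL, but its size there was not simulated separately.

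Radiographic bone fill is untouched. The ambiguity should be settled before the 6-month readings are reduced for analysis, because two of the three secondary outcomes depend on it.

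**What to change.** In Probing Measurements, state that the deepest site at the defect is chosen once, at baseline, and that PPD, relative CAL and relative gingival margin level at 6 months are all taken from that same stent groove, whichever site is then deepest. In Statistical Analysis, state that the between-group comparison of these outcomes is adjusted for the baseline value. Rest conclusions on that comparison, because a fixed deepest site still leaves some regression to the mean in the within-group change.

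The cost is a sentence in each section. Six sites are recorded anyway, so no extra measurement is needed. Baseline data already collected can be re-extracted if the readings were kept by site. If a fixed site was always intended, the change only writes that down.
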